**Sample size**

Sample size justification A pilot study showed the mean TFDi in COVID 19 patients on PEEP 5 and clinically optimal pressure support to be 45% (SD 15); To decrease this by 30% at 36 hours after the dose of morphine with allocation in a 1:1 ratio, 21 patients will be needed in each group.

Compliance and missing data- All analyses will be based on the groups as randomly allocated: an intention-to-treat analysis. A per-protocol analysis will also be done. The statistical significance will be taken as the 5% level for the top comparisons and the subsidiary comparisons, the 1% level. Patients with a P/F ratio > 150 at inclusion will be compared to those with lower values.

Data Storage- Because of the unique challenges of repeated data capture in COVID ICU, all repetitive data will be captured photographically and sent to a central data repository online to be categorized and stored by patient name and time of data capture (once every 8 hours), making in 14-time points of data capture for each patient. Data storage will be by blinded personnel.

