**Sample size**

Sample size justification A pilot study showed the mean TFDi in COVID 19 patients on PEEP 5 to be 45%(SD 15); To decrease mean fractional thickening of the diaphragm index by 30% after the dose of morphine with allocation in a 1:1 ratio, 21 patients will be needed in each group. Accounting for dropouts/ loss of data, 25 patients will be recruited in each limb.

*Statistical analysis*

Interim analyses are planned at 50% of sample recruitment, without unblinding to ensure that subjects are not being exposed to an unacceptable level of risk, whether the trial can be stopped early, check some of the assumptions that went into the original design and sample-size calculations of the trial (like within-group variability, recruitment rates, base event rates). The alpha spending strategy used will be one-fifth of the available 5 percent alpha at the interim analysis. i.e., the interim analysis p-value must be < 0.01 to stop the trial early and claim efficacy. Spend the remaining four-fifths of the 5 percent alpha at the end, or the end analysis p-value must be < 0.04 to claim efficacy. The two groups shall be compared for the mean TFdi (overall and 24^th^ hrly) by unpaired t-tests. Within-group comparison of TFdi shall be made (overall and 24^th^ hrly) by Repeated measures analyses.

Secondary outcomes- Intubation, Mortality, duration of mechanical ventilation, ICU stay, Subjective scores, Demographics, and severity of illness shall be compared by chi-square, t-tests, or nonparametric tests as suitable.

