**Respiratory Drive and related parameters**

Once at baseline and once every 8 hours after that, the following will be assessed till the epidural catheter is in situ, or five days whichever is greater.

The researcher will do the baseline assessment, be aware of the group allocation, and insert the epidural catheter (true or sham). She/ He will mark the site of best visualization for USG probe, ensure best fit NIV interface and assess baseline subjective comfort scores.

After that, all assessments will be done by a fixed set of postgraduate ICU trainees, all trained in TFDi assessment but blinded to group allocation.

Ultrasound-guided TFDi- This procedure will be performed as described earlier.(17,19)

The patient will be supine with head-end elevated to 30 %. The right hand will be abducted and kept near the head. The diaphragm will be located by placing the transducer in the intercostal space above the right 8^th^- 11^th^ intercostal space, in the anterior- axillary line, directing the ultrasound beam perpendicular to the diaphragm. The inferior border of the costophrenic sinus will be identified at end-inspiration as the zone of transition from the lung sliding shadow to the visualization of the diaphragm and liver. The zone of apposition will be noted.

The diaphragm thickness will be recorded in time motion (TM) mode.

The sweep speed will be adjusted to obtain a minimum of three to 8 cycles on the same image.

Several diaphragm images (outlined by the two clear, bright parallel lines of the pleural and peritoneal membranes) will be located: the image will be discarded if the two bright lines are not visible. The least and maximum thickness as on eyeballing will be located and a picture stored for subsequent quantitative analysis and crosschecking by a blinded assessor.

The position of the first (baseline) USG assessment will be marked on the skin to allow all subsequent recordings from the same position.

A note will be made of the ongoing sedation dosages and ventilator settings during the measurement of TFdi (settings will be kept the minimum required for patient comfort – but will not be changed/ dictated for purposes of the study)

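### The sample size names TFdi at 36 hours, the planned tests are overall and 24-hourly, and no text says which comparison decides the primary endpoint

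*Protocol*

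**What the plan says.** The Objectives name TFdi as the primary outcome, with no time point or summary measure.

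The protocol has two Sample size sections. The first reads "To decrease mean fractional thickening of the diaphragm index by 30% after the dose of morphine" and gives no time. The second, at the end of the detailed methodology, reads "To decrease this by 30% at 36 hours after the dose of morphine". Both use a pilot mean of 45% (SD 15), and both conclude that "21 patients will be needed in each group". The first raises this to 25 for dropout.

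Under Statistical analysis in the first section, "The two groups shall be compared for the mean TFdi" by unpaired t-tests, overall and at 24-hourly steps. The same paragraph spends 0.01 at an interim analysis and requires p < 0.04 at the end to claim efficacy. It does not say which p-value.

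The second section adds: "The statistical significance will be taken as the 5% level for the top comparisons and the subsidiary comparisons, the 1% level". It does not say which TFdi comparison is top and which is subsidiary.

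Readings are taken "Once at baseline and once every 8 hours after that" (Respiratory Drive and related parameters). The EPIDURAL section gives up to 96 hours of catheter and 120 hours of observation. The data storage paragraph counts 14 capture points per patient.

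**The concern.** A sample size belongs to a particular comparison. Here the only time point given for it is 36 hours, and no planned test is stated to be at that time. Several comparisons of the same endpoint are listed side by side, under one efficacy threshold that is attached to none of them. Read literally, the plan lets the team decide after seeing the data which TFdi comparison counts. In a trial of about 50 patients with TFdi as its only primary outcome, the main claim could then rest on whichever time point happened to be significant. The false-positive rate would exceed the 5% that the alpha-spending rule is meant to protect.

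**Working it through.** **1. The plan's own figure.** Inputs from both Sample size sections: mean 45, SD 15, a 30% relative fall, 1:1 allocation. Power and sidedness are not stated; I assume 80% and two-sided.

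- Difference: 0.30 × 45 = 13.5 points.
- Normal formula at 5%: n = 2 × (1.960 + 0.842)² × (15/13.5)² = 19.4, so 20 per group.
- Exact t-test: 20 per group gives 79% power and 21 gives 81%, so n = 21, as stated.
- At the final 0.04 level, 21 per group gives 78%. With 25 per group, power is 88% at 0.05 and 86% at 0.04 (85.5% before rounding).

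The figure of 21 is therefore sound for a single two-group t-test.

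**2. Where 36 hours falls.**

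- 36/8 = 4.5. Counted from baseline, the nearest scheduled readings are at 32 and 40 hours.
- 36/24 = 1.5. If the 24-hourly tests are single time points, they fall at 24, 48, 72 and 96 hours, and at 120 if observation runs that long.
- The 36 hours is counted from the dose, the 8-hourly schedule from baseline. The interval between the two is not given. Injections repeat every 18–24 hours (The interventions), and the text does not say which dose starts the clock.

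**3. Number of candidate tests.** Four daily comparisons to 96 hours plus the overall mean make five; five to 120 hours plus the overall mean make six.

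**4. False-positive rate.** If the six tests were independent, the rate would be 1 − 0.95⁶ = 26.5% at 5%, or 1 − 0.96⁶ = 21.7% at 4%. Repeated readings on one patient are correlated, so I simulated five equally correlated z-tests plus the test of their mean, with no true effect. The protocol gives no correlation; the values are assumptions.

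| Assumed correlation | Any test, 5% | Any test, 4% | Overall mean at 5%, daily at 1% | Overall mean at 4%, daily at 1% |
|---|---|---|---|---|
| 0.3 | 21.4% | 17.6% | 7.6% | 6.8% |
| 0.5 | 18.5% | 15.2% | 6.7% | 6.0% |
| 0.7 | 14.9% | 12.2% | 5.8% | 5.0% |
| 0.8 | 12.8% | 10.5% | 5.3% | 4.5% |

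The last two columns give the chance that anything is significant when the overall mean is top and the daily tests are subsidiary. With five tests instead of six, the 4% column runs from about 15% down to 9%.

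**5. Capture count.** 96/8 + 1 = 13 and 120/8 + 1 = 16. Neither is 14.

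**The case against.** Four stronger conclusions are tempting, and the protocol does not support them.

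- *Every test is run at the full level, so the error rate is 15–18%.* The closing section has a 5%/1% rule. If the overall mean is the top comparison, the inflation nearly disappears. The rule is a partial answer only: top comparisons is plural, no TFdi test is assigned to it, and 5% as a final level conflicts with the 0.04 in the other section. It may be meant as the total before the interim share is spent, but that is not said.
- *The powered comparison is never made.* The 24-hourly wording may mean averages over each 24-hour period; Outcome assessment uses daily means for other measures. On that reading the second-day comparison covers 24–48 hours and is centred on 36.
- *No reading can fall at 36 hours.* A dose given 4 hours after baseline would put the 40-hour reading at 36 hours post-dose. Nothing arranges this, but nothing excludes it.
- *The sample size is wrong.* Its arithmetic is right for the planned test method, and nothing in it is specific to 36 hours.

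A separate analysis plan might also set an order among the tests. That would settle which test decides. The protocol would still give one sample size with a time point and once without, and attach its efficacy threshold to no test.

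**Conclusion.** The point holds as a failure to name the decisive comparison, together with a sizing time point that is not aligned with the planned tests. It is not an error in the number of patients, and it is not proof of a particular inflated error rate. The size depends on an assignment the protocol does not make: about 13–21% at 5% (11–18% at 4%) if any of six tests may claim success, against about 5–8% if the overall mean alone is top and daily tests are held to 1%. These ranges rest on assumed correlations of 0.3 to 0.8. The power figures rest on assumed two-sided testing, and the match to 21 also on an 80% power target. Because TFdi is the only primary outcome, the choice should be fixed before any group comparison is seen. The count of 14 captures is a minor inconsistency that affects no test.

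**What to change.** - Name one already planned comparison as the single primary test, for example the between-group difference in overall mean TFdi, and state which readings enter it. Test it at 0.04 at the final analysis, and apply the interim 0.01 to the same comparison.
- Assign every other TFdi comparison to the 1% subsidiary level. Say whether the 24-hourly tests are single readings or 24-hour averages, and reconcile the 5% with the 0.04.
- Rewrite both Sample size sections for the named comparison. Either remove the 36 hours, or define it by a scheduled reading or window with a stated time origin. Keep 21 per group, and state power (about 81% at 0.05 or 78% at 0.04) and two-sided testing.
- Reconcile the 14 capture points with the 8-hourly schedule (13 to 96 hours, 16 to 120 hours).

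The cost is protocol wording, with no extra patients or measurements. The price is that the remaining time points can no longer support a primary claim. Keeping five tests co-primary at 0.05/5 = 0.01 each would be dearer: 31 per group for 80% power by t-test, whereas 21 would give about 59%.

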**The interventions**

A baseline assessment of all outcome measures as appropriate will be made. Normal body temperature, RASS of -1 or 0, and VAS < 4 will be ensured by administering Midazolam ( titrated to effect) or Paracetamol as warranted.

All patients will be turned lateral or sitting position, and an injection of LA be given at L2-3 or L3-4 space. An epidural catheter will be inserted under all asepsis and fixed to the skin in the intervention group. It will be fixed firmly with antimicrobial incise drapes covering at least the lower one-third of the back. For patients who appear fidgety, catheter tunneling may also be used.

The control group will have a sham catheter fixed precisely like the intervention group but not entering the epidural space. The fixation and dressing will be similar to the intervention group.

The intervention group will be administered Injection Morphine Sulphate once every 18-24 hours into the epidural space. The doses will be escalated daily (5-10mg), titrated to the effect: escalation limited by hypoventilation resulting in respiratory acidosis (pH <7.2).

The intervention will continue for a minimum of 2 doses and a maximum of 4 doses (96 hours) of morphine. It will be stopped at 120 hours, or if: the epidural catheter gets dislodged before the second dose, the patient is weaned off noninvasive ventilation to high flow mask for a continuous period of 12 hours or requires endotracheal intubation.

The patient will be followed up till death or 28 days after ICU discharge.

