**Outcome assessment**

*Outcome measures*

TFdi, p0.1, MV, RR, Vt (average of 3 readings, ^eighth^ hourly )

Arterial blood gas and associated values-Pa o2, PaCO2, pH, HCO3, p/F ratio (at least once a day)

Spo2, Fio2, ROX index, Subjective comfort and dyspnea scores – 8^th^ Hourly

VAS, RASS, Weaning (hours off NIV on high flow mask or face mask)- (mean values over 24 hours)

Intubation- Yes/ No: Days after randomization

Length of stay in ICU

Outcome at 28 days of admission

Incidence of excessive respiratory depression (PaCO2> 45 and pH < 7.2)

Incidence of difficult/ failed epidural insertion, catheter pullouts, and complications such as bleeding/ infection/ hematoma will be documented.

Timing of outcome assessment- - Every 8^th^-hour assessment / daily / one time as detailed above

Blinding- The assessor, patient, nurses, physicians, and treating team will be blind to group allocation. One member of the team not involved in research will administer the drug.

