**Reassess Minute volume after 30 minutes.**

- Exclusion: PaCO2 ≥ 45 mmHg *and* pH < 7.2; Compensated respiratory acidosis was accepted up to a pH 7.2 according to standard ARDS lung-protective ventilation guidelines *if GCS >12*

Compensated metabolic acidosis with HCO3 < 16mmol/l with sepsis/ acute or chronic renal failure,

Hemodynamic instability (MAP< 65 mmHg) *and* need of increasing doses of vasopressors in last 6 hrs.; GCS <12;

Contraindication to noninvasive ventilation;

Urgent need for intubation (evaluated by the clinician in charge)

Refusal to participate or participate in another study.

Do-not-intubate decision

Epidural catheter block/ dislodged/ less than two doses of the drug could be administered.

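### A two-dose limit, applied to the per-protocol set or as an exclusion, can remove patients whose harm ended treatment after one dose, and no by-exposure harm analysis is stated

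*Protocol*

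**What the plan says.** The second *Sample size* section (detailed methodology, paragraph on compliance and missing data) sets the analysis sets: "All analyses will be based on the groups as randomly allocated: an intention-to-treat analysis. A per-protocol analysis will also be done". Membership of the per-protocol set is not described, and harms are not treated separately.

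*The interventions* gives the exposure range: "The intervention will continue for a minimum of 2 doses and a maximum of 4 doses (96 hours) of morphine". The events that end the intervention there include dislodgement before the second dose and the patient who "or requires endotracheal intubation". No minimum number of doses is attached to the intubation stop.

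The exclusion list in the detailed methodology (under *Reassess Minute volume after 30 minutes*) contains the item: "Epidural catheter block/ dislodged/ less than two doses of the drug could be administered". This can only be known after randomisation and catheter insertion.

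*Outcome assessment* lists harms among the outcome measures. One is excessive respiratory depression, defined by PaCO2 above 45 with pH below 7.2. The others concern the catheter: "Incidence of difficult/ failed epidural insertion, catheter pullouts, and complications such as bleeding/ infection/ hematoma will be documented". *Safety monitoring and adverse events* says only that adverse effects are recorded and passed to the ethics committee.

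**The concern.** Three statements do not fit together. Analysis is by allocation, yet a patient with fewer than two doses is listed as excluded, and the stopping events in *The interventions* make one-dose patients a foreseeable group. A second analysis is promised on a per-protocol set, and the only dosing threshold from which a reader could build that set is the same two doses.

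For efficacy this is a familiar tension. For harm it matters more, because the number of doses may depend on the harm. A patient who deteriorates after the first dose and is intubated gets no second dose. A two-dose limit then removes the patient because of the event that should be counted. The drug is given to lower respiratory drive, so respiratory depression is the harm a reader will look for first. With 25 patients per arm, one or two removals change the reported rate visibly.

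A smaller issue concerns the denominator. The protocol foresees failed insertion, so some patients allocated to morphine may never receive it. By allocation they still count in the morphine arm.

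**Working it through.** **Arm size.** The plan's 21 per group reproduces: difference 0.30 × 45 = 13.5 points, SD 15, two-sided 5% and an assumed 80% power give 20.4 by the t-test, so 21. Recruitment is 25 per arm, an allowance of 4/25 = 16%. The point does not depend on this calculation; it uses only the 25.

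**Inputs the documents do not give (assumed).** In a morphine arm of 25, let *u* be the number never dosed, *e* the harms among dosed patients, and *k* the harms that followed the first dose and ended treatment. Assume first that all other dosed patients had at least two doses, and that undosed patients have no events.

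- Exposed rate = *e* / (25 − *u*)
- Rate by allocation = *e* / 25
- Rate under a two-dose limit = (*e* − *k*) / (25 − *u* − *k*)

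The last formula is the same whether the limit defines the per-protocol set or is applied as an exclusion from every analysis.

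| *e* | *u* | *k* | Exposed | By allocation | Two-dose limit |
|---|---|---|---|---|---|
| 5 | 2 | 1 | 5/23 = 21.7% | 5/25 = 20.0% | 4/22 = 18.2% |
| 5 | 2 | 2 | 21.7% | 20.0% | 3/21 = 14.3% |
| 5 | 2 | 3 | 21.7% | 20.0% | 2/20 = 10.0% |
| 2 | 2 | 2 | 2/23 = 8.7% | 2/25 = 8.0% | 0/21 = 0% |

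**Dilution by allocation.** With risk *r* in dosed patients and background risk *b* in undosed patients, the rate by allocation is [(25 − *u*) × *r* + *u* × *b*] / 25. For *r* = 20% and *b* = 0, one undosed patient gives 24 × 0.20 / 25 = 19.2%, and four give 21 × 0.20 / 25 = 16.8%. With *b* = 5% the results are 19.4% and 17.6%.

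**Direction.** The two-dose limit also removes *m* patients who had one dose and no harm, for instance after a dislodged catheter. The rate is then (*e* − *k*) / (25 − *u* − *k* − *m*). With *e* = 5, *u* = 2 and *m* = 4, *k* = 3 gives 2/16 = 12.5%, still well below 21.7%, but *k* = 1 gives 4/18 = 22.2%, slightly above it. The rate is understated only when harm is commoner among one-dose patients than among exposed patients overall. That is plausible if harm ends dosing, but it is not certain.

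**The case against.** **The analysis plan may define a safety set.** That is common, the plan is not shown, and the absence of such a set from a protocol is no defect. This stands. What can be faulted is the blanket wording, which assigns all analyses to two sets, and the exclusion item that contradicts it. One may answer that harms are merely documented and reported, and so lie outside those analyses. But they are listed as outcome measures with incidences, and nothing exempts them.

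**The per-protocol definition is inferred.** This also stands. A patient whose treatment stopped for intubation followed the protocol's own stopping rule and might be counted as compliant. The concern is therefore conditional on the two-dose limit being used.

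**Respiratory depression is not a listed stop.** In *The interventions*, hypoventilation with acidosis limits escalation. The intubation criteria name neither PaCO2 nor pH, although the Glasgow coma scale criterion could be met through respiratory depression. So the route from harm to a single dose runs through intubation, and how often it would occur is unknown.

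**Intention to treat loses nothing.** A reader might infer that both sets understate the harm and tilt the safety conclusion towards morphine. The documents do not support that. Analysis by allocation keeps every one-dose event and gives a valid comparison, and its dilution is small beside sampling error: 5 of 25 has an exact 95% interval of about 7% to 41%.

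**A dosed-only set would miss insertion harms.** Bleeding, haematoma and failed insertion arise from the procedure, including in patients never dosed. This is correct, and the fix must provide for it.

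**Conclusion.** The concern holds in a limited form. The exclusion for fewer than two doses (or a blocked or dislodged catheter) conflicts with intention to treat, and the undefined per-protocol set may inherit the same limit. Applied in either way, it can drop patients whose harm led to intubation after one dose, and so can understate respiratory depression.

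On assumed counts the effect ranges from a few points (21.7% to 18.2%) to more than half of the rate (21.7% to 10.0%). With two harms, both after one dose, nothing remains to report. Dilution under intention to treat is modest, at most from 20% to 16.8% with four of 25 undosed. The documents give no number of undosed or one-dose patients and no harm rate, so none of these figures is a prediction. Confidence is medium: the conflict between the passages is in the text, while its effect on the harm rate depends on how the limit is used.

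**What to change.** 1. Reconcile the exclusion list with the intention-to-treat statement, so that no randomised patient is removed from the analysis for receiving fewer than two doses. This concerns who is analysed, not when treatment stops.
2. Keep intention to treat as the primary set.
3. Add to the paragraph on compliance and missing data: 'Excessive respiratory depression and other adverse events are also reported by treatment received in all patients given at least one epidural morphine or sham injection, whatever the number of doses; insertion and catheter complications are reported in all patients in whom true or sham insertion was attempted.'

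The cost is one edited exclusion item, one sentence and one extra descriptive table. The table uses data already collected, and no further patients are needed.

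### The final primary test has two thresholds, p < 0.04 and 5%, and only the first keeps the overall error within 5% after the 0.01 efficacy look

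*Protocol*

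**What the plan says.** The significance level is set in two places in the protocol.

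- **Sample size, Statistical analysis paragraph.** "Interim analyses are planned at 50% of sample recruitment". The error budget is divided as follows: "The alpha spending strategy used will be one-fifth of the available 5 percent alpha at the interim analysis". In operational terms, "the interim analysis p-value must be < 0.01 to stop the trial early and claim efficacy", and the remaining four-fifths goes to the last analysis, where "the end analysis p-value must be < 0.04 to claim efficacy". The primary test is given as: "The two groups shall be compared for the mean TFdi (overall and 24^th^ hrly) by unpaired t-tests".
- **Second Sample size section (under Detailed methodology), Compliance and missing data paragraph.** "The statistical significance will be taken as the 5% level for the top comparisons and the subsidiary comparisons, the 1% level". This paragraph also sets out the intention-to-treat and per-protocol analyses. It does not mention an interim look, 0.04, or the other section.

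**The concern.** The diaphragm thickening fraction is the primary endpoint, so it must be among the top comparisons. One section tests it at 0.04 at the end and the other at 0.05. If the final p-value is 0.045, the trial is negative by one sentence and positive by the other, and no order of precedence is given. The choice could then be made after the result is known.

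The error rate is also at stake. The Statistical analysis paragraph treats 5% as the whole budget and spends part of it at the interim. Testing at the full 5% at the end, after a look that could already have claimed efficacy, overspends that budget.

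**Working it through.** **Inputs from the protocol.** Overall alpha 5%; interim threshold 0.01; final threshold 0.04 (Statistical analysis) or 0.05 (Compliance and missing data); look at half of recruitment; unpaired t-test; control mean 45 and SD 15; 30% relative reduction; 21 evaluable and 25 recruited per arm.

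**Assumptions, because the protocol does not settle them.** Two-sided tests; one interim look, since only one interim threshold and one time point are given; one primary comparison, tested once at each look; information fraction 0.5.

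**Step 1. The plan's own split.** One-fifth of 0.05 is 0.01, four-fifths is 0.04, and 0.01 + 0.04 = 0.05. The figure reproduces as simple addition (Bonferroni). Addition bounds the overall error at 5% whatever the correlation between the looks.

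**Step 2. Actual overall error.** The final data contain the interim data, so the two test statistics have correlation √0.5 = 0.71. Overall error = 1 − P(|Z1| < c1, |Z2| < c2), bivariate normal, with c1 = 2.576 for p = 0.01.

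| Interim, then final | c2 | Sum of levels | Counted twice | Overall error |
|---|---|---|---|---|
| 0.01, then 0.04 | 2.054 | 5.00% | 0.49% | 4.51% |
| 0.01, then 0.05 | 1.960 | 6.00% | 0.54% | 5.46% |

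**Step 3. Sensitivity.**

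| Setting | 0.01 then 0.04 | 0.01 then 0.05 |
|---|---|---|
| Look at 40% information | 4.61% | 5.57% |
| Look at 60% information | 4.39% | 5.34% |
| Both tests one-sided | 4.43% | 5.38% |
| Simulated t-tests, 12 then 25 per arm | 4.56% | 5.53% |
| Simulated t-tests, 10 then 21 per arm | 4.60% | 5.55% |

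The 0.04 rule stays below 5% in every row and the 0.05 rule exceeds it in every row.

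**Step 4. Price of 0.04 in power.** The difference is 0.30 × 45 = 13.5 points, so d = 13.5/15 = 0.9. The t-test noncentrality is 0.9 × √(n/2): 2.92 for n = 21 and 3.18 for n = 25.

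| Per arm | Power at 0.05 | Power at 0.04 | Loss |
|---|---|---|---|
| 21 | 81.2% | 78.4% | 2.8 points |
| 25 | 87.7% | 85.5% | 2.2 points |

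These are fixed-sample values at the final analysis. Counting rejections at the interim as well, power at 0.04 rises to about 79% with 21 per arm and 86% with 25.

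**Step 5. The level that would use the whole 5%.** Solving Step 2 for an overall 5% gives a final level of 0.0452 at half the information, 0.0441 at 40% and 0.0464 at 60%. These are large-sample values. In simulated t-tests of this size, 0.01 then 0.045 gives roughly 5.0% to 5.1%, and with a look at 40% information the normal calculation gives 5.09%.

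**The case against.** The best defence is that the two sections can be read together. Only the Statistical analysis paragraph speaks about the end analysis. It is explicit, and it calls 5% the budget to be divided. On that reading the later 5% is the overall level and the specific rule governs the general one. This reading is possible and may be what the authors meant. But the later sentence gives the level at which significance is declared and pairs it with 1% for subsidiary comparisons, which is plainly a per-test level. It does not call 5% an overall figure or point back to the split. The defence therefore shows which way to reconcile the sections, not that they already agree.

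It is also fair to say that the numbers are small: the excess is about half a percentage point, and the conflict decides the result only if the final p falls between 0.04 and 0.05. That stands. The case for a change rests on the threshold being fixed twice with different values.

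A reader might infer three stronger criticisms that the protocol does not support:

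- *The 0.01/0.04 split is wrong because it does not give exactly 5%.* It is a valid Bonferroni split. Leaving about half a point of alpha unused is a permissible choice.
- *At 0.04 the trial needs 22 per arm, not 21.* This presumes 80% power, which the protocol never states, and depends on the formula: the t-based calculation gives 21.8 and the normal approximation gives 21. It also overlooks the 25 per arm to be recruited.
- *The final level must be 0.045.* Step 5 shows that this figure depends on when the look takes place and can slightly exceed 5% at these sample sizes, whereas 0.04 does not.

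**Conclusion.** The concern holds as a conflict between two stated thresholds for the primary decision. A final p between 0.04 and 0.05 has no settled interpretation. Of the two rules, only a final test at 5% breaks the protocol's own limit, with an overall error of about 5.5%; the 0.04 rule gives about 4.5% and is sound.

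These rates rest on two-sided testing, a single look at half the information and one primary test. The protocol refers to interim analyses in the plural and plans both overall and 24-hourly comparisons of the primary measure. The figures therefore describe the simplest version of the design; they do not measure its error rate if several of those comparisons could each carry the efficacy claim.

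**What to change.** In the Compliance and missing data paragraph, replace the 5% for the primary comparison with: *overall two-sided 5%, spent as p < 0.01 at the interim and p < 0.04 at the final analysis*. Keep 1% for subsidiary comparisons. The sponsor should confirm that two-sided testing is intended, since the protocol does not say. If the efficacy look is dropped, use 0.05 once and state it in both sections.

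A final level near 0.045 is an optional refinement. If it is wanted, compute it from the information fraction actually reached and check it for t-tests at these sample sizes.

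The cost is a sentence or two, with no extra patients or data, plus the small loss of power in Step 4 relative to testing at 0.05. The change should be made before any comparison by group is seen.
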